### Ethics

Ethical approval for the study has been granted by the Mater Misericordiae University Hospital Institutional Review Board (Ref No. 1/378/1864) and ethical exemption has been accepted by the UCD Human Research Ethics Committee – Sciences (Ref No. LS-E-17-03-[name]). The trial will be performed in accordance with the Declaration of Helsinki [34]. No significant adverse events are anticipated during this trial, but will be monitored and any adverse events that occur will be recorded and reported.

This protocol has been written in accordance with the Standard Protocol Items: Recommendations for Interventional Trials (SPIRIT) Statement [35] (See Additional file 1: ExACT Trial SPIRIT 2013 Checklist). Any significant modifications to the protocol will require a formal protocol amendment, agreed on by the project team and approved by the MMUH Institutional Review Board. Minor administrative changes to the protocol will be documented in a memorandum.

### Data collection methods

Data will be collected via self-report questionnaires at baseline (t_0_), post intervention (t_1_) and at 12-week follow-up (t_2_). Physical activity patterns will be measured objectively using Fitbit Zip™ (available from: http://www.fitbit.com) activity trackers and recorded from 1 week prior to commencing treatment through to completion of the intervention.

#### Baseline

A booklet of self-report questionnaires will be sent to participants via post, in advance of a scheduled face-to-face appointment with the lead researcher. This appointment will take place prior to randomisation and no more than 4 weeks prior to starting the intervention. Participants will be requested to complete the questionnaires at home and return them in person on the day of the appointment, when any questions related to the questionnaires can be clarified. The questionnaires will be checked for missing data by the lead researcher and completed by the participant where possible. The questionnaires will later be given to the trial supervisor who will de-identify and code them. No information about treatment allocation will be included on the questionnaires and they will be returned to the lead researcher who will enter the data in a secure, web-enabled information management system. One week of baseline physical activity data (daily step count, active minutes and distance travelled) will be collected prior to starting the interventions. The Fitbit Zip^TM^ activity tracker will be provided to participants at the baseline appointment, with a request to begin wearing the device at least 1 week prior to commencement of the intervention and to continue wearing it for the full duration of the 8-week intervention. An individual Fitbit account will be created for each participant using a unique email address, purposefully created for the study. Data for each participant will be retrieved remotely by the lead researcher via the Fitbit website.

#### Post intervention follow-up

The treating physiotherapist will provide follow-up questionnaires to all trial participants on the last day of the interventions. The participants will be provided with a private space to complete the questionnaires at the end of the last day and the physiotherapist will not be present with the participants whilst they fill in the questionnaires. The questionnaires will be placed in an opaque envelope and sealed before sending to the trial supervisor by registered post. The trial supervisor will check the questionnaires for missing data and will follow-up by post or with telephone calls to participants where possible. The questionnaires will be de-identified as outlined, before returning to the lead researcher who will enter the data into the electronic database.

#### Twelve-week follow-up

The 12-week follow-up time point has been selected as the primary endpoint for establishing effectiveness of the trial intervention. Participants will be contacted via telephone by the administrative staff in the pain clinic and questionnaires will be administered via post with an enclosed stamped addressed envelope for return to the trial supervisor (CD). The trial supervisor will follow up on any missing data again by telephone and a follow-up letter will be sent to participants who fail to return the questionnaires within 2 weeks. A final reminder telephone call will be made by the administrative staff in the pain clinic to participants who have not returned questionnaires after a further week.

### Blinding

Blinding of patients or the treating health professionals will not be possible due to the nature of the interventions. However, a position of clinical equipoise will be maintained, with patients advised verbally and in the Patient Information Leaflet, that they are being offered one of two treatments that are believed to be helpful for chronic pain but it is not known if one treatment is superior to the other. The lead researcher (MBC) will be blinded to group allocation when entering and analysing the data and the statistician (RS) analysing data will also be blinded. Methods to ensure maintenance of this blinding will include de-identification and coding of questionnaires by the trial supervisor (CD), who will be the only person to have access to the locked codes used for treatment allocation. The trial supervisor will also be responsible for randomisation and follow-up of missing data post intervention and at 12-week follow-up. Day-to-day communication and management of scheduling after randomisation will be coordinated by the administrative staff in the hospital pain clinic. Un-blinding of trial participants will occur only after creation of a final locked analysis dataset when the last patient has provided data at 12-week follow-up.

### Outcomes

The outcome measures included in this trial are based on the IMMPACT recommendations for outcome measures for use in chronic pain clinical trials [36]. A recent systematic review [22] recommended formally defining outcome measures as primary, secondary and treatment process measures in future RCTs featuring ACT.

#### Demographic data

Data collected will include age, gender, education level, relationship status and work status. Details regarding pain history will be collected including diagnosis (if applicable), and duration of pain.

##### Primary outcome

Pain interference at 12-week follow-up has been chosen as the primary outcome based on the IMMPACT recommendations and also a systematic review of ACT for chronic pain, which suggests using a measure of physical or social functioning, rather than pain or emotional functioning as a primary outcome [22]. The 12-week follow-up time point has been specified as the primary outcome as this has been suggested to present a low risk of bias in chronic pain trials [37]. Pain interference will be assessed with the Brief Pain Inventory-Interference Scale (BPIIS). This is a seven-item self-report questionnaire that measures the extent to which pain interferes with functions such as general activity, walking ability, normal work, mood, relations with people, enjoyment of life and sleep. The Brief Pain Inventory (BPI) has been shown to be a valid tool for assessing pain interference, with acceptable internal consistency [38]. Excellent test-retest reliability has been reported in a chronic pain cohort [39] and a reduction of 1 point on the interference scale has been recommended as a clinically meaningful change [40].

##### Secondary outcome measures

We hypothesise that participation in the interventions will influence many health dimensions and the following secondary outcomes will be assessed:

#### Pain intensity: Brief Pain Inventory (BPI) – Pain severity subscale

Pain intensity will be measured with the pain severity subscale of the BPI. Reductions of pain intensity of between 10 and 20% have been reported to represent a clinically meaningful change [40].

#### Patient Global Impression of Change (PGIC) scale

The PGIC scale will measure participants’ perceived level of improvement or lack thereof, due to the intervention. The PGIC has strong clinical relevance to the individual with good face and test-retest reliability [41]. The percentages of participants endorsing each of the responses will be reported as per the IMMPACT recommendations [40].

#### Patient satisfaction with treatment

This will be measured using a single question (question 7) from the Client Satisfaction Questionnaire-8 (CSQ-8), which is designed to measure client satisfaction with services [42]. The question will ask ‘In an overall, general sense, how satisfied are you with the service you have received?’ and four potential responses will be provided (very satisfied, mostly satisfied, indifferent or mildly dissatisfied and quite dissatisfied). The percentages of participants endorsing each of the responses will be reported.

#### Health-related quality of life: EuroQoL (EQ-5D-5 L)

The EQ-5D-5 L assesses quality of life in five dimensions: mobility, self-care, usual activities, pain/discomfort and anxiety/depression. Each dimension is scored out of a possible five levels of severity (no problems, slight problems, moderate problems, severe problems and extreme problems). The digits applied to each dimension are then combined in a five-digit number that describes the respondent’s health state. The EQ-5D-5 L has been shown to have good construct validity and responsiveness in a chronic pain cohort [43]. The EQ-5D-5 L will also be used to generate QALYs (Quality-adjusted Life Years), which will be required for a cost-consequence analysis.

#### Mood: Patient Health Questionnaire-9 (PHQ-9) and General Anxiety Disorder-7 (GAD-7)

Symptoms of depression will be assessed using the PHQ-9 [44], which is a nine-item questionnaire generating scores ranging from 0 to 27. A score of ≥ 10 is indicative of probable depressive disorder. The GAD-7 [45] assesses symptoms of anxiety experienced during the last two weeks. Both questionnaires are validated and commonly used to identify and measure symptoms of depression and anxiety in patients with chronic illness.

#### Health economics

A cost-consequence analysis will be performed and data related to costs and QALYs will be reported alongside outcomes. Patient healthcare resource utilisation data will be collected at baseline and at 12-week follow-up, using a self-report questionnaire that will record concomitant care (general practitioner and other healthcare professional contacts, emergency department visits and number of days of hospital in-patient stays related to pain management), investigations and pain interventions during the preceding 3-month period. The costs of providing the interventions will be calculated in terms of direct contact time with healthcare professionals and QALYs will be generated using the EQ-5D-5 L.

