**Methods/design:**

This prospective, two-armed, parallel-group, single-centre randomised controlled trial (RCT) will assess the effectiveness of a combined Exercise and ACT programme, in comparison to supervised exercise for chronic pain. One hundred and sixty patients, aged 18 years and over, who have been diagnosed with a chronic pain condition by a physician will be recruited to the trial. Participants will be individually randomised to one of two 8-week, group interventions. The combined group will take part in weekly psychology sessions based on the ACT approach, in addition to supervised exercise classes led by a physiotherapist. The control group will attend weekly supervised exercise classes but will not take part in an ACT programme. The primary outcome will be pain interference at 12-week follow-up, measured using the Brief Pain Inventory-Interference Scale. Secondary outcomes will include self-reported pain severity, self-perception of change, patient satisfaction, quality of life, depression, anxiety and healthcare utilisation. Treatment process measures will include self-efficacy, pain catastrophising, fear avoidance, pain acceptance and committed action. Physical activity will be measured using Fitbit Zip^TM^ activity trackers. Both groups will be followed up post intervention and again after 12 weeks. Estimates of treatment effects at follow-up will be based on an intention-to-treat framework, implemented using a linear mixed-effects model. Individual and focus group qualitative interviews will be undertaken with a purposeful sample of participants to explore patient experiences of both treatments.

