#### Analyses of effectiveness of primary and secondary outcomes

Descriptive and inferential statistics will be obtained using the appropriate statistical methods that seek to address our identified objectives. The primary analysis will compare the effect of the interventions on the primary outcome; pain interference at 12 weeks post completion of the intervention. All outcome analyses will be conducted according to an intention-to-treat principle, i.e. all randomised participants will be included in the main analysis and will be analysed as randomised, regardless of protocol adherence. Secondary analysis will include the analysis of the primary outcome post intervention and analysis of the secondary and treatment process outcomes detailed previously post intervention and at 12-week follow-up. Linear mixed models on the outcome measures over time will be fitted to evaluate the effectiveness of both interventions, which intrinsically adjusts for pre-treatment scores. Statistical significance will be assessed from a *p* value < 0.05 from the group by time interaction term. For all tests, two-sided *p* values will be used, which will be reported to four decimal places with *p* values < 0.001 reported as *p* < 0.001. The Bonferroni method will be used to appropriately adjust the overall level of significance for multiple secondary outcomes as applicable. In the case of a significant result, planned contrasts of the group effects at post treatment and at 12-week follow-up will be used to investigate the direction and pattern of effects, and outlined in advance in the SAP. As a key component of the reporting of the analyses of outcomes, the mean changes (irrespective of statistical significance) and correlations of the measures between the assessment time periods will be obtained. An up-to-date version of SPSS will be used to conduct the analyses.

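### The resource-use questionnaire is not given at the end of treatment, so its two 3-month recall windows miss nearly all of the 8-week programme and the wait before it

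*Protocol article*

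**What the plan says.** The Health economics section sets two collection points: "Patient healthcare resource utilisation data will be collected at baseline and at 12-week follow-up, using a self-report questionnaire". The form covers contacts with the general practitioner and other professionals, emergency visits, in-patient days, and "investigations and pain interventions during the preceding 3-month period". The same section costs delivery of the two programmes by professional contact time, and adds that "QALYs will be generated using the EQ-5D-5 L".

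The timing comes from other sections:
- The abstract gives the programme length: "Participants will be individually randomised to one of two 8-week, group interventions".
- Analyses of effectiveness of primary and secondary outcomes places the primary endpoint: "pain interference at 12 weeks post completion of the intervention".
- Baseline limits the wait: "This appointment will take place prior to randomisation and no more than 4 weeks prior to starting the intervention". It also asks participants to wear the activity tracker, issued at that appointment, for at least one week before treatment.
- Data collection methods begins "Data will be collected via self-report questionnaires at baseline" and goes on to name post intervention (t1) and 12-week follow-up (t2). No exception is stated there for the EQ-5D-5L.

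The Secondary objectives list healthcare costs among the outcomes to be compared both after treatment and at 12-week follow-up. The analysis section likewise promises analysis of the secondary outcomes at both points.

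Treatment adherence and other interventions says that routine GP and consultant appointments, medication changes and additional interventions during the trial will be recorded and reported. It names no form and does not mention costing.

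**The concern.** A recall form covers only the period it asks about. With no form at t1, the baseline form closes before treatment starts and the follow-up form reaches back only to about the end of treatment. Concomitant care between those points is not asked for on the costing form in either arm, and an analysis plan written later cannot recover answers that were never collected.

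Two things follow. First, the cost-consequence table could set QALYs that run from baseline to follow-up beside concomitant-care costs covering only the last 12 to 13 weeks. Secondly, the stated comparison of healthcare costs after treatment has no data from this form.

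The measured weeks are also a doubtful stand-in for the unmeasured ones. Participants are asked to avoid other allied-health treatment during the 8 treatment weeks only, so use in that period may differ from use afterwards.

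**Working it through.** The document gives no figure for coverage of the costing period, so there is none to reproduce. The check is calendar arithmetic with week 0 as the start of treatment.

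Inputs:
- Treatment length: 8 weeks (abstract).
- Follow-up: 12 weeks after the end of treatment (analysis section).
- Wait from baseline to start, *w*: 1 to 4 weeks. The maximum is stated in Baseline; the minimum follows from the tracker week there.
- Recall, *r*: 3 months, taken as 12 or 13 weeks (assumption).
- Delay in returning the follow-up form, *d*: 0, or 3 weeks as an example. Twelve-week follow-up provides a letter after 2 weeks and a final call a week later. Recall is assumed to run back from the day of completion.

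Formulas:
- Follow-up completed: T = 8 + 12 + d.
- Recall window opens: S = T − r.
- Treatment weeks missed = the smaller of 8 and S.
- Gap between the two windows: G = S + w.
- Baseline-to-follow-up horizon: H = T + w.

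| w | r | d | S | Treatment weeks missed | G / H |
|---|---|---|---|---|---|
| 1 | 13 | 0 | 20 − 13 = 7 | 7 of 8 | 8/21 = 38% |
| 1 | 12 | 0 | 20 − 12 = 8 | 8 of 8 | 9/21 = 43% |
| 4 | 13 | 0 | 7 | 7 of 8 | 11/24 = 46% |
| 4 | 12 | 0 | 8 | 8 of 8 | 12/24 = 50% |
| 1 | 13 | 3 | 23 − 13 = 10 | 8 of 8 | 11/24 = 46% |
| 4 | 12 | 3 | 23 − 12 = 11 | 8 of 8 | 15/27 = 56% |

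With on-time return the gap is 8 to 12 weeks, or 38% to 50% of the horizon. With return 3 weeks late it is 11 to 15 weeks, or 46% to 56%, and the first 2 to 3 weeks after treatment are lost as well.

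Two sensitivity checks:
- If eight weekly sessions are counted as 7 elapsed weeks from first to last, the on-time range becomes 7/20 = 35% to 11/23 = 48%.
- If the 12 weeks ran from the start of treatment, the window would open at week 0 or earlier (12 − 12 = 0; 12 − 13 = −1) and treatment would be covered. The analysis section rules this out by counting from completion.

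What is recorded for the gap, item by item:
- Programme delivery: costed. Contact time per group is 8 × 3.5 = 28 h for the combined arm and 8 × 1.5 = 12 h for exercise alone.
- GP and consultant appointments, and additional interventions: recorded, with no stated link to the costs.
- Emergency visits, in-patient days, investigations and contacts with other professionals: no stated record.

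**The case against.** The strongest reply is that the treatment period is not empty of cost data, and that is right. A reader might infer that all treatment-period costs are missing. They are not: delivery costs fall wholly within that period and carry the main planned cost difference between the arms. The appointment and additional-intervention records also cover some items on the form, and medication is asked about at every time point under Medication. What remains is the set of items with no stated record, and the missing link from the other records to the costing.

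A reader might also take it as settled that QALYs span the whole period. The document states no QALY horizon. The span is inferred from the three questionnaire points and from the EQ-5D-5L being a secondary outcome, so the mismatch is possible rather than stated.

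A third tempting reading is that the arms would differ most in use during treatment. Nothing in the document supports this. The request to avoid other allied-health care applies to both arms and could narrow differences, and the psychologist's contact is already costed as intervention.

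It can also be said that equal 3-month windows before baseline and after treatment allow a coherent before-and-after comparison of use. That stands, but it is not the post-treatment comparison that the objectives name.

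Finally, the participant schedule figure is not available here and might show a form at t1. If so, it would conflict with the Health economics text, and the two would need reconciling.

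**Conclusion.** The point holds for the resource-use form, not for costs as a whole. As scheduled, the form misses about 7 to 8 of the 8 treatment weeks and the 1 to 4 week wait: about 8 to 12 of 21 to 24 weeks (38% to 50%) with on-time return, and more with late return. This assumes that 3 months means 12 to 13 weeks, that the programme takes 8 elapsed weeks, and that the Health economics text gives the full collection schedule.

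The Secondary objectives and the analysis section promise a post-treatment comparison of healthcare costs that this form cannot supply, so those sections and Health economics must be reconciled. The effect is confined to a secondary, descriptive cost-consequence analysis with no planned cost-per-QALY ratio in the text. The primary outcome and its inference are untouched. The change is worth making because it is cheap and the data cannot be reconstructed later.

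**What to change.** 1. Add the existing resource-use form to the post-intervention booklet, with recall running from the baseline appointment.
2. At 12-week follow-up, ask about use since the end of the programme instead of the preceding 3 months. The two forms then meet at t1 whatever the return date.
3. State whether the records of appointments and additional interventions enter the costs and, if they do, how double counting with the form is avoided.
4. State one horizon, baseline to 12-week follow-up, for delivery costs, concomitant-care costs and QALYs.
5. Bring the Secondary objectives, Health economics and the analysis section into line on when healthcare costs are compared.

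Even the unchanged 3-month form given at t1 would nearly close the gap. Its 12 to 13 weeks cover the 8 treatment weeks and the 4 to 5 weeks before them, leaving about 0 weeks uncovered with on-time follow-up and at most about 3 weeks if follow-up is returned 3 weeks late.

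The cost is one short form on a day when participants already complete a booklet on site, and a minor amendment. Recruitment was still open at publication, so later participants would benefit. Those already past t1 keep the gap and should be flagged in the cost tables.

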#### Medication

Current medications will be recorded at each time point with the BPI, which features a specific question related to medication usage. Any changes to medications will be reported.

#### Adverse events

The occurrence of any adverse events will be monitored by the treating clinicians throughout the 8-week intervention period. Any adverse events that occur will be recorded by the lead researcher and reported with the study results.

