#### Combined Exercise and Acceptance and Commitment Therapy (ExACT)

ExACT is a multidisciplinary pain programme combining exercise and psychological therapy. It is a face-to-face, group-based treatment, with up to ten individuals per group. Participants will attend a total of eight sessions, once per week, with each session lasting 3.5 h. Each day will begin with a 2-h psychology session held in the hospital pain clinic. The sessions will follow the psychological approach Acceptance and Commitment Therapy (ACT) and are designed to promote psychological flexibility through methods that encourage openness, awareness and engagement. The overall aim is to reduce pain-avoidant behaviours, in the service of living a rich and meaningful life [21]. Group discussions, experiential exercises and mindfulness practice (see Table 1) will be led by a psychologist who has been trained in ACT and is experienced in treating chronic pain. The content of the sessions will be adapted from an ACT treatment manual used in a recently published study [29] and available to members of the Association for Contextual Behavioral Science (ACBS) from the website http://www.contextualscience.org/better_living_with_illness. Written supplementary material will be provided each week and participants will be encouraged to spend time reviewing the material at home.

**Table 1 Tab1:** Summary of the content of the Acceptance and Commitment Therapy (ACT) component of the combined intervention

Session	Content
1	Introductions and basic foundations of treatment, present the goal of ACT – shifting focus from pursuit of symptom reduction to improving function
2	Review of previous treatment history – creative hopelessness exercise including primary and secondary suffering Introduce openness as a skill area – acceptance as an alternative to avoidance
3	Recap of acceptance and continued focus on enhancing openness. Introduce process of defusion. Passenger on the bus experiential exercise
4	Focus on engagement: values awareness and assessment Experiential values exercise
5	Further values clarification work Committing to action that improves and enriches one’s life
6	Focus on awareness – contact with the present moment, perspective taking and self-awareness as distinct from fusion with thought content and perception of self
7	Treatment review Walking mindfulness exercise
8	Wrap up and conclusions Relapses and set-backs: preparation not prevention

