#### Standalone supervised exercise

The standalone, supervised exercise programme will also consist of eight face-to-face, 1.5-h sessions delivered by a physiotherapist, on a weekly basis, to groups of up to ten participants. The intervention will mirror the supervised exercise component of the combined treatment as described above.

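### Direct adverse-event collection ends with the 8 treatment weeks, relies on clinicians whose contact time differs between arms, and runs through the blinded lead researcher

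*Protocol article*

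**What the plan says.** The section Adverse events fixes three things. The collector and the window are set together: events "will be monitored by the treating clinicians throughout the 8-week intervention period". The recorder and the output follow: "Any adverse events that occur will be recorded by the lead researcher and reported with the study results".

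The only other statement is in the section Ethics: "No significant adverse events are anticipated during this trial, but will be monitored and any adverse events that occur will be recorded and reported". It gives no collector, instrument or time window. None of the outcomes listed for the post-intervention (t1) or 12-week (t2) booklets is an adverse-event question.

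The arms differ in contact time. In ExACT, "Participants will attend a total of eight sessions, once per week, with each session lasting 3.5 h", and of that time "Each day will begin with a 2-h psychology session held in the hospital pain clinic"; the rest is the physiotherapist's class. The control programme "will also consist of eight face-to-face, 1.5-h sessions delivered by a physiotherapist, on a weekly basis".

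The section Blinding states that the treating professionals cannot be blinded. It keeps the lead researcher blind to allocation for data entry and analysis, and gives post-randomisation communication to the clinic's administrative staff. The trial supervisor runs the randomisation and holds the allocation codes.

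**The concern.** Three features of the stated rule work against usable harms data.

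- **The window is short.** Clinician monitoring ends with the last session, but the trial runs on to a primary endpoint 12 weeks later. Participants are encouraged to exercise at home or in a local pool, and the final session prepares them to stay active. A strain or fall in that period has no direct route into the adverse-event record.
- **The opportunity to report differs by arm.** If events surface mainly because someone mentions them to a clinician, the arm with more clinician time can show more events at the same true rate. Adverse events reported from a two-arm trial will be read by arm, whether or not a test is planned.
- **The route crosses the blind.** A report from the psychologist, or about something that happened in an ACT session, identifies the arm, and the named recorder is the lead researcher.

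At stake are the credibility of the harms report and one part of the blinding. The primary efficacy result is not at stake.

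**Working it through.** The article gives no adverse-event rate, so there is no stated figure to reproduce. The sample size (64 per group; 64 / 0.8 = 80 after 20% attrition) does not depend on adverse events and plays no part here.

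**1. Window**

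Inputs: an 8-week intervention (Interventions) and a primary endpoint 12 weeks after its completion (Analyses of effectiveness of primary and secondary outcomes).

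- Treatment start to primary endpoint: 8 + 12 = 20 weeks.
- With direct adverse-event monitoring: 8 / 20 = 40%.
- Without it: 12 / 20 = 60%.

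**2. Contact time**

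| | ExACT | Control |
|---|---|---|
| Weekly contact days | 8 | 8 |
| Physiotherapist | 8 × 1.5 = 12 h | 8 × 1.5 = 12 h |
| Psychologist | 8 × 2 = 16 h | 0 h |
| Total | 8 × 3.5 = 28 h | 12 h |

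The ratio of total hours is 28 / 12 = 2.33. The whole difference is the 16 h of group psychology.

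**3. What unequal contact could do (illustration only)**

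Assume that each contact hour has the same independent chance of bringing an event to light, and that the true event rate is 20% in both arms. Neither assumption comes from the article. If control detects a proportion d of events in 12 h, ExACT detects 1 − (1 − d)^(28/12) in 28 h. For d = 0.5 this is 1 − 0.5^2.33 = 0.80, so the observed rates are 0.2 × 0.5 = 10.0% and 0.2 × 0.80 = 16.0%.

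| Detected, control | Detected, ExACT | Observed, control | Observed, ExACT | Ratio |
|---|---|---|---|---|
| 30% | 56% | 6.0% | 11.3% | 1.9 |
| 50% | 80% | 10.0% | 16.0% | 1.6 |
| 70% | 94% | 14.0% | 18.8% | 1.3 |
| 90% | 99.5% | 18.0% | 19.9% | 1.1 |

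The ratio approaches 2.33 only when detection in control is close to zero. It is 1 if detection does not depend on hours at all.

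**4. Other information collected, and what it covers**

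- Health economics: at 12 weeks, both arms report healthcare contacts, emergency visits, in-patient days, investigations and interventions over the previous 3 months. The recall roughly spans the 12-week gap. The questionnaire records use of care, its in-patient item is tied to pain management, and an event managed at home would not appear.
- Medication: drugs are recorded at each time point, with no link to an event.
- Treatment adherence and other interventions: routine appointments, medication changes, additional interventions and, where possible, reasons for absence are recorded.
- Participant identification, recruitment and consent: reasons for withdrawal are recorded where possible.

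None of these is described as adverse-event collection or linked to the adverse-event record.

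**5. Blinding**

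The section Adverse events makes the lead researcher the recorder of what treating clinicians notice. The section Blinding keeps that person unaware of allocation for data entry and analysis. Nothing in the article says that the reports are stripped of their source first.

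**The case against.** The strongest reply is that the article promises little about adverse events, so little can be wrong. Events are to be recorded and reported. They are not among the objectives, and no between-arm test is planned. The physically demanding component is the same in both arms, with equal physiotherapist time and the same session checklists. Serious consequences would probably show in the healthcare-use questionnaire. Routing details belong in a full protocol.

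Much of this stands, and it rules out several stronger readings:

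- *Nothing is observed after treatment.* A reader might infer this from the 8-week limit. The healthcare-use and medication items are identical in both arms and give some indirect information. The 60% refers to direct adverse-event collection only.
- *People who stop attending are lost to view.* Reasons for absence and withdrawal are sought where possible, and missing questionnaires are followed up by post or telephone. What is absent is a link from these records to adverse events.
- *A promised comparison is biased 2.3-fold.* No formal comparison is promised, and 2.33 is the ceiling of an assumption. The article offers no evidence on how detection depends on hours.
- *The blind is broken.* The article does not say what the reports contain. Outcomes are self-reported, and a separately blinded statistician runs the outcome analyses. The document supports a risk of disclosure, not a certainty.

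The appeal to a condensed article does not remove the core point. The article does not leave the method open: it names the collector, the window and the recorder. The general wording in Ethics adds nothing to them.

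**Conclusion.** The point holds as a design weakness in harms reporting, of low to moderate priority. Direct adverse-event collection covers about 8 of the 20 weeks to the primary endpoint. It depends on unblinded clinicians with 28 h of contact in one arm and 12 h in the other. The likely direction of any distortion is more events found in ExACT. That is an inference from contact time, and its size is unknown: the illustration gives observed ratios from 1.1 to 1.9, within limits of 1 and 2.33, all under assumed detection rules. The conflict between the recording role and the lead researcher's blinding needs no assumption about event rates, but actual unblinding depends on what the reports disclose. The primary efficacy analysis, the sample size and the error rates are unaffected.

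**What to change.** 1. Add one identical self-report adverse-event item to the t1 and t2 booklets in both arms, covering the period since the previous booklet. Base any by-arm summary on it.
2. List clinician-noted events separately, labelled as such, and do not use them to compare the arms.
3. Send clinician reports to the trial supervisor, who already holds the allocation, and release them to the lead researcher only once the dataset is locked. The supervisor already de-identifies the booklets, so free-text answers that reveal the arm can be held back or coded at the same step.
4. Make sure the t1 booklet reaches participants who are absent from session 8. It is handed out on the last day of the intervention, and the item is most needed for those who stopped attending.
5. Align the wording in Ethics and Adverse events so that both give the same collector and window.

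The cost is one item in two booklets already in use and a short amendment. The downside is a slightly longer questionnaire and more minor events to tabulate. For participants already past t1 or t2 when the change is made, the item would be missing, and the report should say so.
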